## Abstract

**Methods/design::**

This is a multicenter, two parallel-group, single-blind, randomized controlled trial. Eighty-eight subjects with KOA (Kellgren Lawrence grade II or III) will be recruited and randomly treated with smokeless moxibustion or traditional moxibustion in the ratio of 1:1. The smokeless moxibustion group will use plant herbal activated carbon smokeless moxa cone. The traditional moxibustion group will be treated with pure moxa cone. Subjects in both groups will receive treatment at the affected knee(s) at the acupuncture point ST35, EX-LE2, and EX-LE4. Subjects in both groups will receive 3 sessions per week of moxibustion for 4 weeks. The primary outcome are changes in the Western Ontario and McMaster Universities Osteoarthritis Index pain scores from baseline to week 24. Secondary outcomes include visual analog scale, 50 yards fast walking time, short-form heath survey 36, overall clinical efficacy evaluation, self-assessment of safety, treatment credibility and expectancy, and cytokines related to osteoarthritis in serum.

**Discussion::**

This randomized single-blind controlled trial takes traditional moxibustion as the control group to provide strict evidence for the clinical efficacy and safety of herbal activated carbon smokeless moxibustion in the treatment of KOA.

## 1. Introduction

Knee osteoarthritis (KOA) is a chronic inflammatory disease with high incidence rate, ranks 11th in the global disability diseases. With the aging of the world population and the aggravation of obesity, the demand for medical treatment of KOA has substantially increased.^[1]^ Knee trauma, cold and humid environment, bad living habits, age and obesity are the risk factors of knee arthritis.^[2–7]^

The guidelines published by the Osteoarthritis Research Society International in 2019 propose a combination of drug and non-drug treatment as a method of non-surgical treatment.^[8]^ The existing medications for inflammatory pain have obvious side effects. Currently, there is no therapeutic method of complete cure for osteoarthritis. The treatment is limited to the relief of symptoms, so as to improve the quality of life and activity.^[9–11]^ It is also reported that chondroitin and glucosamine can slow down the injury of knee cartilage, but cannot reduce the pain.^[12,13]^ The effect of hormone injection is similar to that of physical therapy in the short term.^[14]^

Effective intervention on KOA may reduce knee pain, prevent complications, and even help to reduce mortality.^[15]^ Traditional moxibustion is a widely used characteristic treatment technology of traditional Chinese medicine, which is often used to treat KOA.^[16–18]^ However traditional moxibustion has some defects like time-consuming and laborious, the flame is easy to cause ambustion, and the treatment room also has many requirements. In particular, the smoke generated in the combustion process is not conducive to the health of physicians and patients which to a certain extent restricts its clinical application. The mechanism of moxibustion is related to its warm effect and radiation effect. The previous study of our research group found that the combustion temperature of plant herbal activated carbon smokeless moxibustion is close to that of traditional moxibustion. Infrared radiation characteristics peak of two kinds of moxibustion are similar to that of human acupoints deducting blackbody radiation and adenosine triphosphate energy metabolism, and can resonate with the molecules in acupoints and body tissues to produce curative effect, providing the physiological physics basis that smokeless moxibustion can be used as an alternative material for traditional moxibustion. It has been reported that infrared radiation has effects on cellular adenosine triphosphate metabolism, cyclooxygenase concentration, and bone repair.^[19,20]^ The efficacy of herbal active carbon smokeless moxibustion in the treatment of KOA has not been evaluated in clinical trials. The hypothesis is that 3 sessions per week of 2 kinds of moxibustion will have the clinical effect on KOA.

## 2. Method

### 2.1. Study design

This is a non-inferiority randomized single-blind controlled clinical trial, which aims to compare the treatment of typical inflammatory pain (KOA) with herbal activated carbon smokeless moxibustion and traditional moxibustion. The protocol has been registered in the Chinese Clinical Trial Registry (No. ChiCTR2200057923) and will be implemented in accordance with the declaration of Helsinki. Eligible participants will be randomly divided into 2 groups (new smokeless moxibustion group or traditional moxibustion group), with a distribution ratio of 1:1. The whole study will include 4 weeks of treatment and an additional 20 weeks of follow-up. The patient will be informed: You will have a 1 in 2 possibilities of receiving smokeless moxibustion or traditional moxibustion. Prior to randomization, written consent should be obtained from each participant.

An overview of the study process is shown in Figure 1.

**Figure 1. F1:**
[figure not shown]
Study flow chart.

### 2.2. Study setting, recruitment, and ethics

The recruitment will be conducted in the outpatient department of acupuncture and moxibustion of Shanghai Municipal Hospital of Traditional Chinese Medicine Affiliated to Shanghai University of traditional Chinese medicine, Longhua Hospital Affiliated to Shanghai University of traditional Chinese medicine, and Shuguang Hospital Affiliated to Shanghai University of traditional Chinese medicine. A total of 88 subjects with KOA will be enrolled. This study has been approved by the medical ethics review committee of Shanghai Municipal Hospital of Traditional Chinese Medicine (No.2022SHL-KY-13). Recruitment will be carried out through social platforms, clinics, community publicity, etc. The investigators will contact those who may be willing to participate in this study by telephone, conduct preliminary screening according to the inclusion and exclusion criteria, and then arrange for a clinical physician to conduct a face-to-face baseline visit at an appropriate time, meanwhile performing radiological evaluation on subjects. The investigator will introduce the study protocol (i.e., study objective, procedure and time commitment, potential risks and benefits related to the study) to potential subjects in detail, and obtain written informed consent. The subject’s privacy information will be protected. Each subject will be given a unique random number as a direct identifier of the case report.

### 2.3. Inclusion criteria

Age 40 to 75 years.According to the diagnostic criteria of KOA of the American rheumatology society.^[21–25]^Radiographic confirmation of KOA (Kallgren Lawrence grade ≥ 1).^[26–28]^Moderate or more severe knee pain for most of the past month; the subject’s visual analog scale baseline score for arthritic pain is 40 points and above.Agree to accept the random assignment, understand, and be willing to sign the informed consent form.

### 2.4. Exclusion criteria

Knee pain caused by other diseases such as rheumatoid arthritis, fibromyalgia syndrome, chronic fatigue syndrome, and ankylosing spondylitis.Received steroids in the past 3 months.Received acupuncture treatment within 3 months.Hyaluronate was injected into the joints in the past 6 months.History of joint puncture or arthroscopy in the past year.History of the knee/hip replacement surgery or planning to perform such surgery during the trial.Use of other topical treatments, such as topical use of drugs.Presence of any serious diseases including heart disease, lung disease, kidney disease, liver disease or malignant tumor, systemic infection or infectious disease, and mental illness.Participation in another clinical study in the past 1 month.

### 2.5. Withdrawal criteria

Subjects who drop or discontinue prior to completion of the treatment period should conduct a questionnaire survey and those who have serious adverse reactions will be reported to the ethics committee.

Those who have not completed the treatment and have withdrawn before the end of treatment.Any serious adverse reactions.Major problems in the protocol design or trial process (such as those who are seriously infected due to blistering).

### 2.6. Randomization

A total of 88 subjects with KOA who are eligible per protocol will be randomly assigned to group A plant herbal activated carbon smokeless moxibustion group or group B traditional moxibustion group in a 1:1 ratio. After the investigator and the subject sign the informed consent, the investigator will perform a simple rheumatic examination. The investigator will make a diagnosis based on the knee X-ray film brought by the subject or the knee X-ray performed at the site. Only the subject who meet the inclusion/exclusion criteria will be randomized by a random number table. Then investigator will make a baseline assessment and arrange treatment.

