### 2.11. Outcomes

If the subject had a single knee joint pain, the outcome assessment will be evaluated for that knee. If both knees were affected and only one of them met the inclusion criteria, only the eligible knee will be evaluated. If both knees met the inclusion criteria, select the knee with more pain for evaluation.

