### 2.12. Primary outcome indicators

The primary outcome measure is the change in pain relative to baseline at the Western Ontario and McMaster Universities Osteoarthritis Index (WOMAC) from baseline to week 24. The most painful knee joint for the subject will be recorded at the baseline, which will be the joint we measured throughout the trial. We will also measure WOMAC pain at week 2, 8, 12, and 24.

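### Section 2.6 puts the baseline assessment after randomisation, against sections 2.2 and 2.3, and nothing places the baseline WOMAC pain score of the primary outcome before allocation

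*Protocol article*

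**What the plan says.** Section 2.6 gives the steps in order: consent, a simple examination, diagnosis from a knee X-ray, then "Only the subject who meet the inclusion/exclusion criteria will be randomized by a random number table", and then "Then investigator will make a baseline assessment and arrange treatment".

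Other sections bear on the timing of baseline:

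- Section 2.2 has the investigators screen by telephone and then "arrange for a clinical physician to conduct a face-to-face baseline visit at an appropriate time", with radiology at the same time. WOMAC is not mentioned there.
- Section 2.3 requires that the subject's "visual analog scale baseline score for arthritic pain is 40 points and above".
- Section 2.12 defines the primary outcome as the change in WOMAC pain from baseline to week 24, and adds: "The most painful knee joint for the subject will be recorded at the baseline, which will be the joint we measured throughout the trial".
- Section 2.11 adds the rule for two eligible knees: "If both knees met the inclusion criteria, select the knee with more pain for evaluation".
- Table 1 ticks WOMAC, VAS, SF-36 and serum markers in a first column headed *Before treatment*.
- Section 2.17 compares the change in WOMAC pain between arms by t test.

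On blinding, section 2.10 describes subjects as blinded and treats the two arms in separate rooms. Section 3 says that the operator learns the group before placing the box, and that operators are trained in assessment as well as treatment.

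**The concern.** A baseline value is a fair starting point for a change score only if allocation cannot have influenced it. Read as written, section 2.6 gives up that protection: the assessment follows randomisation and is made by the person who then arranges treatment. Sections 2.2 and 2.3 suggest that some baseline data already exist by then, so the article does not give one consistent order.

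The primary outcome is at stake. If recorded baseline pain were higher in the smokeless arm because of allocation, and follow-up scores were unaffected, the excess would appear as extra improvement. In a non-inferiority trial that works towards a positive conclusion. A shift in the other direction would cost power.

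**Working it through.** **Step 1: the order, item by item.**

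| Item | Placed before randomisation? | Source |
|---|---|---|
| X-ray and eligibility | Yes | 2.2, 2.6 |
| VAS of at least 40 | Yes, because it is an entry criterion | 2.3 |
| Baseline visit | Yes, but its content beyond radiology is not given | 2.2 |
| Baseline assessment by the investigator | No, it follows randomisation | 2.6 |
| WOMAC pain at baseline | Not stated; Table 1 says only *Before treatment* | 2.12, 2.15 |
| Recording of the index knee | At baseline, so the same uncertainty applies | 2.12 |

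The Table 1 heading fits either order, because treatment starts after randomisation in both. No text settles when baseline WOMAC pain is taken, and the only explicit sequence, in section 2.6, puts the baseline assessment second.

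**Step 2: who could be influenced.** Subjects are described as blinded. No text shields the investigator. The investigator's knowledge of the arm at baseline is inferred from three points: the subject-only blinding, the arranging of treatment by the same person, and the separate rooms by arm.

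**Step 3: the index knee.** Section 2.11 leaves three cases: one painful knee, two affected knees of which one is eligible, and two eligible knees. Eligibility settles the first two before randomisation. Only the third leaves a choice.

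**Step 4: how a shift enters the estimate.** Let improvement be baseline minus week 24, and let b be an allocation-related excess in recorded baseline in the smokeless arm that does not recur at week 24. The expected difference in mean improvement (smokeless minus traditional) becomes the true difference plus b.

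**Step 5: illustration of size.** Inputs from section 2.16: margin 10% × 184.87 = 18.49, one-sided α = 0.025, power 80%, 38 per arm. No SD is given, so the 38 cannot be reproduced forwards. Solving backwards with true difference zero:

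SD = 18.49 / [(1.960 + 0.842) × √(2/38)] = 28.8.

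Any SD from about 28.4 to 28.8 rounds up to 38 by the normal formula; the t-based range is about 28.0 to 28.4. I use 28.4, and add 60 and 100 as assumed values to show the range.

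With the true difference at the margin (−18.49), the chance of wrongly declaring non-inferiority is Φ(b/SE − 1.960), where SE = SD × √(2/38). The shifts are chosen as about a quarter and a half of the margin: 18.49/4 ≈ 4.6 and 18.49/2 ≈ 9.2.

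| SD | SE | b = 0 | b = 4.6 | b = 9.2 |
|---|---|---|---|---|
| 28.4 (back-solved) | 6.52 | 2.5% | Φ(−1.25) ≈ 10% | Φ(−0.55) ≈ 29% |
| 60 (assumed) | 13.76 | 2.5% | Φ(−1.63) ≈ 5% | Φ(−1.29) ≈ 10% |
| 100 (assumed) | 22.94 | 2.5% | Φ(−1.76) ≈ 4% | Φ(−1.56) ≈ 6% |

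**The case against.** The strongest reply has four parts.

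First, a reader might infer that the investigator definitely knows the arm when recording baseline. The article does not say so. Section 3 attributes that knowledge to the operator, and sections 2.7 and 2.10 give treatment to trained operators. This stands: knowledge of allocation is plausible and nothing prevents it, but it remains an inference.

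Second, WOMAC looks largely self-completed. At week 24 the questionnaire is mailed and filled in by subjects, who are described as blinded, so an investigator has limited power to move the score. This also stands. It limits the likely bias without removing it, because section 2.6 assigns the baseline assessment to the investigator.

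Third, sections 2.2 and 2.3 show that some baseline work precedes randomisation, so actual practice may be sound. That is possible. However, neither section mentions WOMAC, and if practice is sound then section 2.6 describes it wrongly.

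Fourth, the 10% and 29% could be taken as expected error rates. They are not. They depend on a back-solved SD and on shifts chosen for illustration, and they fall to between 4% and 10% at the larger SDs.

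Two further readings are tempting and unsupported. The mention of a random number table does not establish simple, unrestricted randomisation: restricted lists can be drawn from such a table, and blocks, strata and concealment are details that an article commonly leaves to the full protocol. Nor can one conclude that subjects will be lost between randomisation and baseline, since no interval between the two is stated.

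**Conclusion.** The point holds as an inconsistency in the stated sequence that reaches the primary outcome. Section 2.6 puts the baseline assessment after randomisation, sections 2.2 and 2.3 put baseline elements before it, and no section secures baseline WOMAC pain before allocation. The resulting risk is a possible bias, conditional on the investigator knowing the arm and on the shift being absent at week 24. The exposure of the index knee is confined to subjects with two eligible knees, and even there the more painful knee may already be known from screening.

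For the shifts illustrated, false non-inferiority runs from about 4% to 29% depending on the SD, against a nominal 2.5%. The article gives no basis for saying that a shift of any particular size will occur. It is still worth correcting, because the t test on change described in section 2.17 would carry such a shift straight into the result, and a starting value not exposed to allocation cannot be recovered afterwards.

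**What to change.** Rewrite section 2.6 in a single order: consent; X-ray and eligibility; baseline WOMAC, VAS, SF-36, serum sample and index knee all completed and locked; then randomisation and disclosure of the allocation. State in section 2.2 that these measures are taken at the baseline visit. Reconcile sections 2.3 and 2.12 with this order, and head the first column of Table 1 *Before randomisation* for these items.

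The cost is protocol wording and, if practice follows section 2.6 today, a reordered visit. It needs no extra subjects and leaves the sample size unchanged. If sites already take baseline first, only the text needs correcting.

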### 2.7. Interventions

The treatment scheme of this experiment is based on the clinical treatment of KOA with traditional moxibustion, combined with blinding, considering the standardization requirements of the experimental design.

According to the literature review, the following 3 acupoints are selected as therapeutic acupoints. ST35, EX-LE2, and EX-LE4 are all located in the knee region, and they are common acupoints in the global clinical research of treating KOA.^[29]^ In anatomy, acupoints ST35 and EX-LE 4 are located close to the thinnest part of the knee joint, so the warm effect of moxibustion can directly reach the joint cavity. According to biomechanical study, most of the clinical diagnosis and treatment guidelines of KOA pay special attention to muscle strength training of quadriceps femoris.^[30–33]^ The muscle strength of the extensor and flexor groups of the knee joint is closely related to the symptoms of KOA.^[34]^ EX-LE2 is near the medial oblique and lateral femoral muscles, which can directly improve the state of the quadriceps femoris.

Subjects are allowed to take concomitant medication, but we will encourage them not to change their medications during the trial. However, other therapies such as acupuncture and sodium hyaluronate injection are not allowed.

The whole treatment process will be supervised by the staff of the study team. The two groups of subjects will be treated separately by strictly trained treatment operators.

### 2.8. New smokeless moxibustion group

The smokeless moxibustion group will a new smokeless moxa cone (1.5 * 2.0 cm, combustible for 20 minutes) produced by Jiangsu Sancai Wuyan Medical Technology Development Co., Ltd. will be used After the moxa cone is ignited, it is put into the moxibustion box and fixed on the acupoints. If the subject feels scorching hot, adjust the temperature by adjusting the height of the moxibustion box to avoid empyrosis.

### 2.9. Traditional moxibustion group

After the moxa cone is ignited, it is put into the moxibustion box and fixed on the acupoints. If the subject feels scorching hot, adjust the temperature by adjusting the height of the moxibustion box to avoid empyrosis.

Treatment of 2 groups will last for 20 minutes, 3 times a week, and altogether 12 times in 4 weeks (every Tuesday, Thursday, and Saturday). If the subject is unable to receive treatment on time, he or she will be required to complete the treatment within that week.

If any adverse event occurs, treatment will be suspended, and the investigator can decide whether to terminate the treatment.

### 2.10. Treatment blinding

Both smokeless moxibustion and traditional moxibustion are placed in an unmarked moxibustion box after ignition. Their appearance and operation procedures are the same. The combustion of moxa sticks in the box is invisible. The masked description used in the consent is as described in the “method/design and setting” above so that the subjects will be blinded until the completion of the study. The whole process is supervised by the coordinator of our study team in each center. All subjects in the study will be treated by trained operators. Due to the difference in the amount of smoke burned by the 2 kinds of moxa sticks, subjects of 2 groups will be treated in separate treatment rooms to avoid communication.

### 2.11. Outcomes

If the subject had a single knee joint pain, the outcome assessment will be evaluated for that knee. If both knees were affected and only one of them met the inclusion criteria, only the eligible knee will be evaluated. If both knees met the inclusion criteria, select the knee with more pain for evaluation.

### 2.12. Primary outcome indicators

The primary outcome measure is the change in pain relative to baseline at the Western Ontario and McMaster Universities Osteoarthritis Index (WOMAC) from baseline to week 24. The most painful knee joint for the subject will be recorded at the baseline, which will be the joint we measured throughout the trial. We will also measure WOMAC pain at week 2, 8, 12, and 24.

### 2.13. Secondary outcome indicators

The most important secondary outcome measurement is the improvement of WOMAC function. We will also assess the total score, function score, and stiffness score of WOMAC at baseline, week 2, 4, 8, 12, and 24. Visual analog scale pain score will be used to evaluate the arthritis pain of subjects at baseline, week 2, 4, 8, 12, 24. Short-form health survey 36 will be used to measure the quality of life of the subjects. In addition, we will evaluate the efficacy of a 5-point scale in the 4th week (1 = very poor, 2 = poor, 3 = general, 4 = OK, 5 = very good).

Any adverse event, whether related to treatment, requires the subject and investigator to report on each treatment or visit. Side effects included redness and blistering caused during treatment in both groups. Serious adverse events will be reported to the Ethics Committee. During the follow-up period (week 5–24), we will call the subject weekly to find out about the adverse reactions and side effects that may occur during the week.

After 4 weeks of treatment, the investigator will ask the subjects about the safety of the treatment including safe, fewer safe, safety problems, and serious safety problems. After each treatment, we will ask the subject’s feelings: “What do you feel during the treatment? 1. Heat; 2. Cold; 3. Pain; 4. no feeling; 5. Other, please describe.” The subjects will be allowed to take the analgesic or non-steroidal anti-inflammatory drugs used before the test, we will ask subjects to record the daily dose during the entire clinical trial, and then analyze the changes in the dose. We will measure the outcome of the baseline, week 2, 4, 8, and 12 at the investigation center. For the outcome of week 24, we will mail the questionnaire to the subjects and ask them to post them back after filling them out.

